### Intervention protocols

Laparoscopic-assisted radical resection of distal gastric cancer will be performed by an experienced surgical team from the 13 centres listed in Table 1. Each of these centres performs at least 100 gastric cancer operations per year. Lymph node resection will be performed under laparoscopy, the main anastomosis will be performed with the assistance of a small incision, and the abdominal incision will be less than 8 cm. According to the research programme, the experimental group will actively carry out pre-rehabilitation before the operation, including lifestyle intervention, exercise advice, diet guidance, and health education (outpatient and hospitalization individualized condition consultation and answer). The specific interventions are shown in Table 2. However, target-oriented liquid management and early enteral nutrition (EN) after surgery require special attention. The goals of goal-directed therapy are to maintain central euvolemia while avoiding excess salt and water and a 24-h postoperative fluid balance on + 1 to 1.5 L. Intraoperative detection indicators are as follows: blood pressure, cardiac output, estimated blood loss, end-tidal carbon dioxide, and heart rate. The maintenance fluid flow rate is 1~4 mL kg^− 1^ h^− 1^ (predicted body weight), and large deviations from “zero balance” should be avoided [20]. The well-defined principles for oral intake in the ERAS groups are as follows: drinking a small amount of water and chewing xylitol on the day of operation; drinking 500~1000 mL water and chewing xylitol on postoperative day 1 (POD1); oral EN (mainly polypeptide) and chewing xylitol on POD2; oral EN (mainly integrin type) and chewing xylitol on POD3; oral EN, a small amount of semifluid and chewing xylitol on POD4; oral EN, semifluid (mainly) and chewing xylitol on POD5, but the patients in the traditional treatment group began sequential EN support treatment in accordance with the dietary pattern of the ERAS group after anal exhaust.

**Table 2 Tab2:** Perioperative pathway management for gastric cancer

Programme components		ERAS group	Traditional treatment group
Preoperative	***Health education, exercise advice, dietary guidance**	Yes	Yes
	***Organ function evaluation**	Yes	Yes
	***Pre-rehabilitation treatment**	Yes	No
	***MDT, clinical decision making**	Yes	Yes
	***Preoperative nutritional assessment and intervention**	Yes	Yes
	**Intestinal preparation**	EN No mechanical bowel preparation	No Traditional mechanical intestinal preparation
	***Preoperative fasting and abstinence from drinking**	Fasting 6 h before the operation 2-h oral glucose infusion 200 mL	Fasting and drinking for 6 h before the operation
Intraoperative	***Intraoperative safety check (Checklist)**	Yes	Yes
	**Local anaesthesia in the deep layers of the incision at the end of surgery**	Local anaesthesia (30 mL 0.25% bupivacaine)	No
	**Prevention of antibiotic use**	30 min before operation, operation time > 3 h, or more than one bleeding event ≥ 1000 mL	Application for 1–2 days
	***Surgical incision**	Small midline (< 8 cm) incision at the upper abdomen	Small midline (< 8 cm) incision at the upper abdomen
	***Precision surgery**	Laparoscopic or robotic surgery	Laparoscopic or robotic surgery
	***Anaesthesia mode**	General anaesthesia combined with epidural anaesthesia^a^ (T7–T9)	General anaesthesia
	**Intraoperative heat**^**b**^**preservation**	Yes	Yes
Postoperative	**Urinary catheter**	Removal within 24 h	Routine indwelling catheter for 1–3 days after operation (until the patient is ambulatory and can urinate on his own)
	**Abdominal drainage tube**	Avoid placement or removal early after the operation as much as possible	Removal before discharge^c^
	**Gastric tube**	No use or removal ≤ 24 h	Retention for 1–3 days^d^
	***Early bedside activity**	Start cautiously and plan your activities	2–3 days after operation
	***Postoperative analgesia**	Multimodal analgesia^e^	Opioids^f^
	***Target-oriented liquid management**	Yes	No
	**Prevention of deep venous thrombosis**	Basic prevention + physical prevention + drug prevention	Drug prevention
	***Early EN after operation**	Sequential EN treatment after awakening from anaesthesia	Gradually start EN after anal exhaust

* Core provisions of perioperative enhanced recovery after surgery (ERAS) pathway management

*Abbreviations*: *EN* enteral nutrition, *MDT* multidisciplinary team, *NSAID* non-steroidal anti-inflammatory drug

^a^Dose/drug: 500 mg of ropivacaine + 400 mg of lidocaine and liquid intake rate of 2 mL/h

^b^Heat preservation measures: Pre-heated fluid replenishment, thermal blanket, heater

^c^Extubation indication: The drainage fluid is light red or clear, with a volume of less than 20 mL, and pancreatic amylase is negative for 24 h

^d^Criteria for the removal of nasogastric tube: Recovery of intestinal peristalsis, anal exhaust and oral intake of clear fluids

^e^Multimodal analgesia: postoperative day 1~2 (POD1~2) patient controlled epidural analgesia (lidocaine + ropivacaine); POD3~5, 0.65 g of regular oral paracetamol every 8 h (q8h); when the visual analogue scale ≥ 4, 50 mg of flurbiprofen is injected intravenously

^f^Opioids: POD1~2, 50 mg of tramadol q8h; when the visual analogue scale ≥ 4, 50 mg of tramadol is injected intravenously (dose ≤ 400 mg/d)

### Study endpoints

The main endpoint is the comparison of 3-year overall survival (OS) and disease-free survival (DFS) between the ERAS pathway group and the traditional treatment group. The secondary endpoints are the total incidence of postoperative complications, incidence of major complications, 30-day re-hospitalization rate, 30-day mortality rate, hospitalization days and hospitalization costs as well as other short-term clinical outcomes. The exploratory results are changes in inflammatory indexes (i.e., leukocytes, neutrophil percentage, CRP, procalcitonin, TNF-α and IL-6).

### Data collection and management

Once written informed consent is provided, the clinical researchers will collect baseline data such as age, sex, body mass index, and complications. The laboratory indexes—routine blood, liver and kidney function, electrolyte, carcinoembryonic antigen, carbohydrate antigen 199 (CA199), CA724, CA242, alpha fetoprotein (AFP), hepatitis, human immunodeficiency virus, syphilis, blood coagulation routine, and blood type—will also be assessed and recorded before and during hospitalization. The designated surgeon will record the details of the procedure, such as the surgical approach, the location of the tumour, lymph node metastasis, and pathological stage.

Starting on day 1 after the operation, the clinical observation data (e.g., extubation time, food intake, activity, anastomotic leakage, first exhaust and defecation time, postoperative hospital stay, and complications) will be recorded daily by nurses to evaluate postoperative recovery. Clinicians will be responsible for patient management and will not be involved in data collection.

All relevant information for each patient should be recorded in the CRF in a timely and accurate manner by trained and independent research staff. If there are any errors in the CRF, the investigator will correct them immediately. When revising raw data, the investigator must sign their name and the date. All data will be acquired only by study investigators who have signed a confidential disclosure agreement. In this clinical study, any collected information that could be used to disclose an individual’s identity will not be released or disclosed at will without consent, except in special circumstances as required by law. No research publications using these data, including journal literature, papers or research briefs, will use any identifying patient information. The ethics committee of the Affiliated Hospital of Qingdao University will be responsible for ensuring that the rights and well-being of patients are protected and for maintaining compliance with the currently approved protocol, data collection, statistical analysis, and anonymity in publications.

### Discharge criteria

The criteria for discharge are as follows: (1) postoperative pain score with oral analgesics controlled well (visual analogue scale score below 4), (2) oral semifluid food without intravenous rehydration, (3) satisfactory exercise regimen (6 h a day or up to preoperative level), (4) adequate out-of-hospital care, (5) voluntary discharge of the patient, and (6) no surgical complications, such as fever, abdominal pain, or infection. In addition, the contact information and address of each patient will be confirmed before discharge. Follow-up will be conducted by telephone within 24 h after discharge, and the focus will be on dietary tolerance, pain, defecation and any discomfort.

### Follow-up

After the operation, a special follow-up team will be responsible for performing patient follow-up, and the first outpatient review will begin at 3 weeks after the end of treatment.

From 0~2 years after the operation, follow-up every 3 months will include a routine blood examination, an analysis of biochemical markers and digestive tract tumour indicators, and imaging examinations. In addition, endoscopic examinations will be performed once a year. At each follow-up, the adjuvant treatment, postoperative recovery, and short-term and long-term side effects will be assessed, as shown in Fig. 2. From 2~3 years after the operation, follow-up will occur every 6 months, as outlined above.

**Fig. 2 Fig2:**
[figure not shown]
Flowchart of the multicentre clinical trial for the schedule of enrolment, interventions and assessments. The symbol “×” indicates the project that must be completed during the research phase; −1, 2 weeks before operation; 0, perioperation; 1, adjuvant chemotherapy time; follow-up 2~11 corresponding time points are the following: 2, 3 months after operation; 3, 6 months after operation; 4, 9 months after operation; 5, 12 months after operation; 6, 15 months after operation; 7, 18 months after operation; 8, 21 months after operation; 9, 24 months after operation; 10, 30 months after operation; 11, 36 months after operation.

### Statistical analyses

Classification variables will be analysed by the chi-squared test or Fisher’s exact test, and continuous variables will be analysed by the independent *t* test. DFS will be defined as the time from surgery to death or recurrence of gastric cancer, whichever occurs first. The Kaplan–Meier method will be used to generate survival curves, and the log-rank will be applied to compare the differences between survival curves. The hazard ratio and 95% confidence interval will be calculated with the Cox regression model. Variables will be selected for inclusion in the final multivariable model using a stepwise method, and significance levels of 0.25 and 0.15 will be employed as the criteria for inclusion and retention. A *P* value of less than 0.05 will be considered to indicate statistical significance. Data analysis will be performed by using SPSS® software package version 22.0 (SPSS Inc., Chicago, IL, USA).

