### Perioperative management

Before surgery, chest computed tomography (CT), total abdominal enhanced CT, and pelvic CT will be performed to confirm the size and location of the tumour, and distant organ metastasis will be excluded according to evaluations by two experienced radiologists. Upper abdominal CT angiography will be used to evaluate variation in the gastric blood supply of the patients, reduce the risk of intraoperative bleeding and guide lymph node dissection [19]. Echocardiography and pulmonary function tests will be used to evaluate the tolerance of cardiopulmonary function to laparoscopic surgery.

Laparoscopic-assisted radical resection of distal gastric cancer will be performed under general anaesthesia. During the operation, we will follow the basic principles of tumour treatment, master the appropriate scope of gastrectomy, perform fine lymph node dissection and gastrointestinal reconstruction, and record the amount of intraoperative infusion, blood loss, operation time, and use of any opioids or muscle relaxants.

After the operation, any adverse reactions that occur will be closely observed and actively treated. All drugs used will be recorded and described on the case report form (CRF). Laboratory examinations will be performed before the operation and 2 , 4 and 7 days after the operation. The measurements will include routine blood, liver and kidney function, electrolytes, procalcitonin, CRP, IL-6 and TNF-α. For patients with pathological stage II or above, 6–8 cycles of S-1 capsule combined with oxaliplatin adjuvant chemotherapy will be performed. Finally, oncology experts will choose the scheme and duration of treatment in accordance with the actual situation of the patients.

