### Sample size estimate

This study adopts the design of a non-inferiority test, and the calculation of sample size is based on the following historical data and assumptions. Previous studies have shown that the overall 3-year survival rate for patients with gastric cancer is about 50% [5]. The centre followed patients who underwent radical resection of gastric cancer under the management of ERAS from 2011 to 2014, and the 3-year survival rate was about 65% [21]. Given that patient selection will require 10 months, the median follow-up time should be about 3 years, and therefore the non-inferiority threshold is set to 1.33, according to a 1:1 random ratio. Given a significance level of α = 0.05 (bilateral) and test efficiency of 1 − β = 80%, the withdrawal rate of either branch group should be 10% and thus the total sample requires at least 400 patients (200 in the test group and 200 in the control group).

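### Plain t tests for the exploratory inflammatory markers give up precision that adjustment for the scheduled pre-operative value would recover

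*Protocol article*

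**What the plan says.** The Statistical analyses section of the protocol article names one method for all continuous outcomes: "continuous variables will be analysed by the independent" t test. It mentions no covariate, transformation or rank-based alternative for them. Categorical variables do get a fallback, Fisher's exact test.

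On timing, Perioperative management states: "Laboratory examinations will be performed before the operation and 2 , 4 and 7 days after the operation". On content it adds: "The measurements will include routine blood, liver and kidney function, electrolytes, procalcitonin, CRP, IL-6 and TNF-α". Leukocyte count and neutrophil percentage come from the routine blood test, so all six markers have a planned pre-operative value and three planned post-operative values.

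Study endpoints ranks the markers as exploratory and words them as changes: "The exploratory results are changes in inflammatory indexes". It does not say which day counts or how change enters the test. The secondary endpoints include "hospitalization days and hospitalization costs as well as other short-term clinical outcomes"; stay and cost have no pre-operative counterpart.

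**The concern.** The design pays for a baseline and three follow-up samples per patient, and the named test makes poor use of them. An independent t test on day-2, day-4 or day-7 values ignores the baseline. A t test on changes uses it, but forces its coefficient to be exactly one. Neither treats the three days together.

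What is at stake is precision on the marker comparison. The outcome is exploratory but not incidental: the abstract lists inflammatory indexes among the results the trial should clarify, and the Background and Discussion offer a reduced stress and inflammatory response as the reason why ERAS might improve survival. A wider interval than necessary makes that part of the story harder to read.

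**Working it through.** **Inputs from the protocol article.** There are 200 patients per arm (Sample size estimate: "the total sample requires at least 400 patients (200 in the test group and 200 in the control group"). A 10% withdrawal rate leaves 200 × 0.9 = 180 per arm. The two-sided level is 0.05. The article gives no standard deviation, effect size or power for any continuous outcome, so there is no figure of the plan's own to reproduce.

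**Assumed inputs.** The correlation r between pre- and post-operative values is taken as 0.3, 0.5 and 0.7. The standard deviation (SD) is first taken as equal before and after surgery.

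**Step 1: variance of the treatment difference, with the post-value t test set to 1.**

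- Change-score t test: 2(1 − r).
- ANCOVA: 1 − r².
- ANCOVA relative to change score: (1 − r²) / [2(1 − r)] = (1 + r)/2.

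| r | Change score | ANCOVA | ANCOVA / change score |
|---|---|---|---|
| 0.3 | 1.40 | 0.91 | 0.65 |
| 0.5 | 1.00 | 0.75 | 0.75 |
| 0.7 | 0.60 | 0.51 | 0.85 |

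Multiplying by 400, ANCOVA matches a post-value t test on 400 patients with 364, 300 and 204 patients. It matches a change-score t test on 400 with 260, 300 and 340.

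**Step 2: power.** The difference that gives a post-value t test 80% power with 200 per arm is (1.960 + 0.842) × √(2/200) = 0.28 SD.

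| r | Post-value t | Change-score t | ANCOVA |
|---|---|---|---|
| 0.3 | 80.0% | 65.8% | 83.5% |
| 0.5 | 80.0% | 80.0% | 89.9% |
| 0.7 | 80.0% | 95.1% | 97.5% |

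Below r = 0.5, with equal SDs, change scores do worse than ignoring the baseline.

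**Step 3: where the gain shrinks.** At r = 0.1 and 0.2, ANCOVA variance is 0.99 and 0.96 of the post-value t test, which is almost no gain. The change-score comparison also depends on the ratio k of post- to pre-operative SD. The change-score variance is then 1 + 1/k² − 2r/k, in units of the post-operative variance. With k = 5 (assumed):

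- r = 0.3: 1 + 0.04 − 0.12 = 0.92; ratio 0.91/0.92 = 0.99.
- r = 0.5: 1 + 0.04 − 0.20 = 0.84; ratio 0.75/0.84 = 0.89.
- r = 0.7: 1 + 0.04 − 0.28 = 0.76; ratio 0.51/0.76 = 0.67.

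So when surgery inflates the spread, a change score behaves much like a post-value. The large gain shown for r = 0.3 under equal SDs then all but disappears.

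**Step 4: skew.** Lognormal data were simulated with 180 per arm and 10,000 runs. The log-scale SD σ was set at 0.4, 0.8 and 1.2, and the true shift at 0.28σ on the log scale.

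| σ | Type I error, raw t | Power, raw t | Power, log t |
|---|---|---|---|
| 0.4 | 4.7% | 73% | 76% |
| 0.8 | 5.1% | 61% | 75% |
| 1.2 | 4.5% | 48% | 76% |

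The raw-scale t test keeps its level. If values are skewed and effects multiplicative, it loses power.

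**The case against.** **The article is condensed and the SAP is not shown.** Transformation, repeated measures and missing laboratory values are commonly settled in an SAP, so their absence here is no finding. That stands. What remains reviewable is the method the article does state for every continuous variable.

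**A t test on changes already uses the baseline.** The endpoint wording allows that reading, so it cannot be said that the baseline is ignored. Even so, ANCOVA has variance no larger than either t test, and the loss remains unless the slope of post-operative on baseline value happens to be one (or, against post-values, r is zero).

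**The size is assumed.** This stands. A reader might take from r = 0.5 that the plan wastes the equivalent of one third more patients (400/300). That is one point in a range that reaches almost nothing.

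**The baseline may not be clean.** The laboratory schedule fixes the sample only as pre-operative, while Table 2 gives pre-rehabilitation to the ERAS arm alone. A late sample could already carry a treatment effect, and adjusting for it could remove part of what is being measured. A change score would share that problem. This stands as a condition on the fix.

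**Stronger readings that the documents do not support:**

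- *The day-7 comparison is biased.* The ERAS diet is mainly semifluid by postoperative day 5, controls start the sequence only after anal exhaust, and "oral semifluid food without intravenous rehydration" is a discharge criterion. Earlier ERAS discharge and more missing day-7 samples are therefore plausible. But day 7 is scheduled for all, semifluid intake is one of six criteria, and no text says that sampling stops at discharge. No missing fraction is given.
- *Skewed outcomes are wrongly tested or poorly summarised.* The article states no distribution and no summary statistic. Type I error holds at this size, and the mean is a legitimate target for cost.
- *The baseline argument covers stay and cost.* Neither has a pre-operative value.

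**Conclusion.** The point holds as a matter of efficiency for the exploratory marker outcomes. Assigning a plain t test to them gives up precision whether it is applied to post-operative values or to changes. Under assumed r of 0.3 to 0.7 and equal SDs, adjustment removes 9% to 49% of the variance of a post-value t test and 35% to 15% of that of a change-score t test. The gain over post-values is 4% or less for r up to 0.2. Over change scores it is about 1% at r = 0.3 if the post-operative SD is five times the baseline SD. The true r and SD ratio are not in the documents.

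The primary survival comparisons, by log-rank and Cox regression, are untouched, and no test is invalid. This is a worthwhile improvement of modest weight.

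**What to change.** Replace the blanket t test, for the six markers only, with ANCOVA at each day or, better, one repeated-measures model over days 2, 4 and 7. Use the log scale for markers that are skewed. Include arm, day, arm-by-day, the pre-operative value, and the two minimisation factors (site, and laparoscopic or robotic procedure). State that the baseline is a sample taken before randomisation, or at least before pre-rehabilitation starts, and check that sites draw it then. The repeated-measures model also uses day-2 and day-4 values from any patient whose day-7 sample is missing.

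For hospital days, a rank-based analysis, and for cost, a bootstrap interval around the mean difference, may be added as supportive analyses. They are options and correct no error.

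The cost is slightly more analysis work and the check of baseline timing. No extra patients are needed, and no extra samples if the pre-operative draw already falls early enough. If it does not, moving that draw is a small operational change.

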### Sample size estimate

This study adopts the design of a non-inferiority test, and the calculation of sample size is based on the following historical data and assumptions. Previous studies have shown that the overall 3-year survival rate for patients with gastric cancer is about 50% [5]. The centre followed patients who underwent radical resection of gastric cancer under the management of ERAS from 2011 to 2014, and the 3-year survival rate was about 65% [21]. Given that patient selection will require 10 months, the median follow-up time should be about 3 years, and therefore the non-inferiority threshold is set to 1.33, according to a 1:1 random ratio. Given a significance level of α = 0.05 (bilateral) and test efficiency of 1 − β = 80%, the withdrawal rate of either branch group should be 10% and thus the total sample requires at least 400 patients (200 in the test group and 200 in the control group).

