## Abstract

**Background:**

The incidence of gastric cancer in East Asia is much higher than the international average. Therefore, improving the prognosis of patients and establishing effective clinical pathways are important topics for the prevention and treatment of gastric cancer. At present, the enhanced recovery after surgery (ERAS) pathway is widely used in the field of gastric surgery. Many randomized controlled trial (RCT) studies have proven that the ERAS regimen can improve the short-term clinical outcomes of patients with gastric cancer. However, a prospective study on the effect of the ERAS pathway on the prognosis of patients with gastric cancer has not yet been reported. This trial aims to confirm whether the ERAS pathway can improve the disease-free survival and overall survival of patients undergoing laparoscopic-assisted radical resection for distal gastric cancer.

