**Discussion:**

The results of this RCT should clarify whether the ERAS pathway is superior to traditional treatment on inflammatory indexes, short-term clinical outcome and survival for laparoscopic-assisted radical resection of distal gastric cancer. It is hoped that our data will provide evidence that the ERAS pathway improves survival in patients with gastric cancer.

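### The sample size section declares a non-inferiority design with a threshold of 1.33, but the stated aim and the planned test are about superiority, and nothing says which criterion decides success

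*Protocol article*

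**What the plan says.** Under Sample size estimate, the protocol article states "This study adopts the design of a non-inferiority test". After giving the accrual period and the median follow-up, it continues: "therefore the non-inferiority threshold is set to 1.33, according to a 1:1 random ratio". The scale of 1.33 is not named. The Trial design section also lists an inferior value among the inputs to the sample size.

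The purpose is worded differently elsewhere. The abstract's Background says "This trial aims to confirm whether the ERAS pathway can improve the disease-free survival and overall survival of patients", and its Discussion expects the results to "clarify whether the ERAS pathway is superior to traditional treatment on inflammatory indexes, short-term clinical outcome and survival". The limitations section and the main Discussion also speak of improving prognosis or survival.

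Under Statistical analyses, "the log-rank will be applied to compare the differences between survival curves", with P below 0.05 as the rule. A Cox hazard ratio with a 95% confidence interval is planned, but its limit is not compared with 1.33.

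**The concern.** A non-inferiority result and a superiority result support different claims. Excluding an HR of 1.33 shows that ERAS is not worse by more than the margin. It does not show that ERAS improves survival, which is the question asked. Conversely, a non-significant log-rank test does not establish non-inferiority.

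The article contains the ingredients of both designs and does not say which decides success, or that one is tested after the other. The margin, as printed, follows from accrual time and follow-up. Those determine how many deaths are observed, not how much loss of survival is acceptable. At stake are the headline claim on the main endpoint and whether 400 patients suit the declared design.

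**Working it through.** **Inputs (Sample size estimate).** Threshold 1.33; two-sided alpha 0.05; 80% power; 1:1 allocation; 10% withdrawal per arm; historical 3-year survival about 50% (gastric cancer patients) and about 65% (one centre's ERAS patients); total 400.

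**Assumptions not in the document.** 1.33 is a hazard ratio; hazards are proportional; 50% is the control arm and 65% the ERAS arm, so HR = ln 0.65 / ln 0.50 = 0.621. Evaluable patients: 400 × 0.90 = 360. Deaths: 360 × 0.35 = 126; 360 × 0.425 = 153; 360 × 0.50 = 180; without withdrawal, 400 × 0.50 = 200.

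**1. Reproducing 400 under the declared design.** D = 4(z_α + z_β)² / (ln 1.33 − ln HR_true)², with (1.960 + 0.842)² = 7.849 and (ln 1.33)² = 0.0813.

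- True HR 1: 4 × 7.849 / 0.0813 gives 387 deaths. At 50% survival, 387 / 0.50 = 774, and 774 / 0.90 = 860 patients. At 65%, 387 / 0.35 = 1,106, and 1,106 / 0.90 = 1,229.
- True HR 1, one-sided 0.05: 305 deaths, or 678 to 969 patients. Modelling 10 months of accrual with exponential survival lowers this to 620 at the least.
- True HR 0.621: 55 deaths; 55 / 0.425 = 130, and 130 / 0.90 = 145 patients.
- Power with 360 evaluable and true HR 1 is Φ(ln 1.33 / SE − 1.96), with SE = 2/√D: 48% with 180 deaths, 36% with 126.

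None of these gives 400.

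**2. Superiority on 50% versus 65%, two-sided 0.05, 80% power.**

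- Schoenfeld: 4 × 7.849 / (ln 0.621)² = 139 deaths; 139 / 0.425 = 328; 328 / 0.90 = 365.
- Freedman: 145 deaths; 342; 380 after withdrawal.
- Two proportions: 340; 378 after withdrawal. With continuity correction: 366; 407 after withdrawal.

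With 360 evaluable patients (153 deaths), log-rank power at HR 0.621 is about 84%.

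**3. Where the two criteria part.** Superiority requires an observed HR below exp(−1.96 SE). Non-inferiority requires one below 1.33 × exp(−1.96 SE). If the true HR is 1, the chance of meeting non-inferiority without superiority is Φ(ln 1.33 / SE − 1.96) − 0.025.

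| Deaths | SE | Superiority if HR below | Non-inferiority if HR below | Chance at true HR 1 |
|---|---|---|---|---|
| 126 | 0.178 | 0.705 | 0.938 | 33% |
| 153 | 0.162 | 0.728 | 0.969 | 40% |
| 180 | 0.149 | 0.747 | 0.993 | 46% |
| 200 | 0.141 | 0.758 | 1.008 | 50% |

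**4. What the margin would tolerate.** 0.50^1.33 = 0.398, about 10 points below 50%. 0.65^1.33 = 0.564, about 9 points below 65%.

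**The case against.** A reader might infer that the two criteria contradict each other and give opposite conclusions. They do not. They are nested and can be read from the same 95% interval, so an observed HR between the two limits means non-inferior with superiority not shown. Testing non-inferiority against a margin fixed in advance and then superiority would need no alpha adjustment. What stands is that the article does not describe that sequence or name the deciding criterion.

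A reader might also infer that the protocol requires superiority to be shown. The abstract says whether, the Objectives section only speaks of investigating the impact, and no formal null hypothesis is written. The superiority question is read from the stated aim and the planned test.

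The planned Cox interval could serve a non-inferiority test, and the full protocol or analysis plan may link it to the margin or justify the margin better. That is fair for the missing detail. It does not remove the conflict between the design label and the aim, both of which are printed here.

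Finally, the size argument depends on the hazard ratio reading. A comparison of proportions with a 15-point non-inferiority margin would need 354 to 389 patients after withdrawal. The article states no such margin, but its possibility means that the origin of 400 cannot be proved.

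**Conclusion.** The point holds as a contradiction in the current text: a non-inferiority label and threshold stand beside a superiority question and a test of difference, with no stated criterion for success. This does not depend on any calculation.

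The size of the problem does rest on assumptions: 1.33 as a hazard ratio, proportional hazards, and 126 to 200 deaths. On these, observed HRs from about 0.71–0.76 up to about 0.94–1.01 would be non-inferior without superiority shown. If ERAS had no effect, such a result would occur in roughly 33% to 50% of trials. With a true HR of 1, the declared design needs about 860 to 1,230 patients at two-sided 0.05. If HR 0.62 is taken as the truth, it needs only about 145.

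The 365 to 407 patients needed for superiority are consistent with 400. A reader might conclude that 400 was calculated for superiority, but the article does not assign 50% and 65% to the arms, so this is suggested and not shown. Nor does anything in the article indicate an intention to choose the criterion after seeing the data; the text merely leaves that open.

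**What to change.** Restate the Sample size estimate section as a superiority design: null hypothesis HR = 1, two-sided alpha 0.05, log-rank test, planning values of 50% (control) versus 65% (ERAS) 3-year overall survival, HR about 0.62 under proportional hazards. Remove the non-inferiority wording and the 1.33 threshold, and remove the inferior value from the Trial design section. State that a non-significant result will be reported as inconclusive, not as non-inferior.

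For a single endpoint this leaves the size at 400. The cost is that a non-inferiority claim is given up. It is also more than an editorial change: enrolment was ongoing at submission, and the interim section says that results go to all investigators. The amendment must therefore be dated and documented before any comparative outcome data are seen.

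Keeping non-inferiority would also be coherent, but at greater cost. It would need a justified margin on a named scale, a test of the confidence limit against it, a changed aim and, on the hazard ratio reading with true HR 1, a much larger trial.

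This change does not settle how overall survival and disease-free survival are to be combined as the main endpoint. That is a separate matter.
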